#### Study arms

##### Intervention components

The GPs in the intervention group receive the PPI deprescribing intervention tools and materials at the start of follow-up. The intervention is designed for the Swiss primary care setting and includes specific materials and tools for both GPs and trial participants (figure 1). It was developed to address the barriers and enablers of PPI deprescribing at patient and GP levels, and the materials were co-designed and adapted based on patient and GP feedback.^25^,^28^ For GPs, the intervention includes an initial digital and printable teaching module that provides comprehensive knowledge and skills related to PPI medications and the deprescribing process. This is followed by an online training session featuring interactive role plays to simulate various GP-patient scenarios. Additional material includes a laminated infographic, a consultation script and a deprescribing decision tree, all designed to assist GPs in guiding participants through the PPI deprescribing process. GPs will also be provided with a brochure to give to the trial participants (patients). This brochure contains information about PPIs, an explanation of the deprescribing process, a list of evidence-based alternative strategies to manage potential rebound symptoms and an invitation to use a digital symptom diary to self-monitor their symptoms and experiences throughout the trial. The digital diary requires internet access and a connection to the calendar on a cell phone or computer. For participants without internet access or a cell phone, a paper-and-pencil version of the symptom diary will be available.

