#### Secondary endpoints

The secondary endpoints are multifaceted: total number of medications prescribed during the trial measured using unique Anatomical Therapeutic Chemical codes, reduction of at least 50% of the prescribed PPI dose, PPI discontinuation (defined as a stop in PPI prescription as indicated by the GP), PPI sustained discontinuation (defined as 3 months without prescribed PPI), a switch to on-demand use, or use of alternative anti-reflux treatments, individual components of the RDQ (regurgitation, heartburn, dyspepsia) and atypical gastrointestinal symptoms measured by the Reflux Symptom Index (RSI).^31^ The RSI scales for each individual item ranges from 0 (no problem) to 5 (severe problem) points, with a maximum of 45 points. Further, we are interested in the occurrences of additional safety outcomes such as ulcers and/or gastrointestinal bleedings, nutritional deficiencies due to PPI overuse, such as vitamin B12, iron, magnesium or sodium, as well as other comorbidities, such as osteoporosis, small intestinal bacterial overgrowth, anaemia, fractures, nephritis and intestinal infections as reported by the GP. Furthermore, we will measure the QoL using the European Quality of Life-5-Dimensions 5-Levels (EQ-5D-5L) questionnaire.^32^ Each of the five dimensions (mobility, self-care, usual activities, pain/discomfort and anxiety/depression) has five levels (no, slight, moderate, severe and extreme problems) out of which one overall utility measure on a scale of 0 (worst health/death) to 1 (perfect health) will be derived using published algorithms.

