#### Blinding procedures

Given the nature of the intervention, blinding of GPs and patients will not be feasible. Thus, this is an open-label trial. However, those in the control group will remain unaware of the detailed nature of the intervention. Also, the study members involved in data collection, data analysis and statistics will not be blinded to the intervention assigned to each study arm, since information on the implementation of the intervention elements will only be collected from the intervention group.

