### Methods: safety monitoring and public and patient involvement

#### Safety monitoring

Collection, reporting and investigation of SAEs, as well as notification to the ethical committee will be conducted following the applicable regulation and approved process. Conversely to SAEs, reporting of non-SAEs is not mandatory and will be done at the discretion of the treating physician.

To ensure the safety of our participants, we plan to conduct one interim analysis after the first 200 participants are followed for at least 6 months after inclusion. The safety parameters that will be considered in this interim analysis include the RDQ, gastrointestinal ulcers, gastrointestinal bleeding and all SAEs in each group. The advisory board will evaluate unblinded data and provide recommendations.

In addition to the trial’s safety monitoring, we have included relevant adverse events within the primary and secondary safety endpoints.

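### One secondary safety outcome, nutritional deficiencies, is worded with a causal condition that an unblinded GP would judge and that the intervention itself alters, so its comparison between arms is open to differential attribution.

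*Protocol article*

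**What the plan says.** Under Secondary endpoints, the protocol article names several additional safety outcomes. One is "nutritional deficiencies due to PPI overuse, such as vitamin B12, iron, magnesium or sodium". The items that follow are plain occurrences: "as well as other comorbidities, such as osteoporosis, small intestinal bacterial overgrowth, anaemia, fractures", and then "nephritis and intestinal infections as reported by the GP". Ulcers and gastrointestinal bleedings, which open the list, also stand without a causal qualifier. Only the deficiency item has one.

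Under Blinding procedures, the article states that "blinding of GPs and patients will not be feasible". Under Intervention components, intervention GPs receive a "teaching module that provides comprehensive knowledge and skills related to PPI medications and the deprescribing process", plus an online session with role plays. Under Usual care, control GPs have no access to these components.

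Under Data collection, GPs in both arms complete online surveys at baseline and at 3, 6, 9 and 12 months, which cover medications and diagnoses among other items.

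**The concern.** A randomised comparison of an adverse outcome needs an event that is defined the same way whatever the arm. Here the wording adds a causal judgement to the event. The only reporter named is the GP, who knows both the allocation and the current prescription.

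The judgement is also tied to the treatment. All participants enter with inappropriate PPI use, and the intervention aims to end it; the first co-primary endpoint measures how far it succeeds. A clause that asks whether overuse caused the deficiency therefore refers to a state that changes after randomisation and is meant to change more in one arm.

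At stake is the reading of this single outcome. The Introduction cites nutritional deficiencies as a reason for concern about long-term PPI use, and the Discussion says that success could reduce nutrient deficiencies. A lower recorded count in the intervention arm would be taken as support for that, although part of it could come from the wording.

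**Working it through.** The article gives no expected rate, power or threshold for deficiencies, so there is no stated figure to reproduce. The check has a textual part and an illustration on assumed values.

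**Textual part**

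1. *Is there a causal qualifier?* Yes, on the deficiency item and on no other item in the list.
2. *Who would apply it?* The GP, the only reporter named for these outcomes.
3. *Is that person blinded?* No. Data collectors and analysts are not blinded either: "the study members involved in data collection, data analysis and statistics will not be blinded to the intervention".
4. *Does the treatment affect the judgement?* Yes. Stopping the PPI removes the presumed cause. The Discussion also expects that some participants will receive new diagnoses that justify a PPI; for them, continued use is arguably no longer overuse.
5. *Does the article name a safeguard for this item?* No. It acknowledges open-label bias in general terms, and its Limitations discuss contamination, over-the-counter use and symptom over-reporting, but not GP attribution.

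**Illustration**

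Let q be the true risk of a deficiency, equal in both arms, and let s be the probability that a true deficiency is recorded as an event. The observed risk is q × s, so the observed risk ratio (intervention to control) is s_int / s_con, whatever the value of q.

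*Counts.* Taking 400 planned participants as 200 per arm and assuming q = 6%, each arm has 200 × 0.06 = 12 deficiencies. Assuming attribution of 80% in control and 40% in intervention:
- control 12 × 0.8 = 9.6
- intervention 12 × 0.4 = 4.8
- ratio 4.8 / 9.6 = 0.5, with no true effect.

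*Chance of a false finding.* With mean cluster size m = 400/80 = 5, the article's coefficient of variation of 0.5 and its intracluster correlation of 0.05 for the effectiveness endpoint (borrowed here), the design effect is 1 + ((0.5² + 1) × 5 − 1) × 0.05 = 1 + 5.25 × 0.05 = 1.26. The effective size is 200 / 1.2625 ≈ 158 per arm. A normal-approximation two-sided 5% test of two proportions then gives:

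| Recorded, control v intervention | Observed ratio | False-finding rate, q = 5% to 15% |
|---|---|---|
| 0.5 v 0.5 | 1.00 | 5% |
| 0.5 v 0.4 | 0.80 | 6% to 8% |
| 0.6 v 0.4 | 0.67 | 9% to 17% |
| 0.6 v 0.3 | 0.50 | 15% to 36% |

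Worked line for 0.6 v 0.3 at q = 10%:
- Observed risks are 0.06 and 0.03, difference 0.03, mean 0.045.
- Null standard error = √(2 × 0.045 × 0.955 / 158.4) = 0.0233.
- Standard error under the difference = √((0.06 × 0.94 + 0.03 × 0.97) / 158.4) = 0.0232.
- Rejection probability ≈ 1 − Φ((1.96 × 0.0233 − 0.03) / 0.0232) = 0.25.

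The rates are the same if the arms are swapped. At q = 5% the expected counts are only 3 to 6 per arm, so the approximation is rough there.

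**The case against.** The strongest reply is that the phrase may not be an operational condition. The list is introduced as outcomes of interest, by way of examples, and the words on overuse may only explain why these deficiencies were chosen. Nowhere does the article instruct GPs to judge causality. The survey wording and case definition may sit in the full protocol or the case report form. This stands as a caution: that deficiencies count only when attributed is the literal reading, not an established procedure. It does not remove the point, because the words are in the endpoint text, a plan that follows them would carry them forward, and if they are only explanatory, deleting them loses nothing.

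Three stronger readings are tempting and are not supported.

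- *Testing differs by arm.* A reader might infer this from the training given to intervention GPs only. The article does not say that the module teaches testing for deficiencies, and its silence on laboratory tests proves nothing in a condensed paper. Differential testing is possible, not documented.
- *Reporting of these outcomes is optional.* A reader might infer this from the statement under Safety monitoring that "reporting of non-SAEs is not mandatory and will be done at the discretion of the treating physician". That sentence concerns adverse-event reporting. The same section says that relevant adverse events are included within the safety endpoints, and GPs in both arms are surveyed about diagnoses on the same schedule.
- *The same defect covers anaemia, osteoporosis, fractures and the rest.* These items carry no causal qualifier.

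It is also fair that the assumed counts would not by themselves make a convincing finding. Rounded to 10 v 5 of 200, Fisher's exact test gives p = 0.29 before any allowance for clustering.

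**Conclusion.** The point holds as a minor one about one secondary safety outcome. Taken literally, the wording makes an unblinded GP's causal attribution part of the event, and the intervention changes the basis for that attribution. The comparison of this outcome between arms is therefore open to differential attribution.

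The size cannot be derived from the article. On the assumed values above, a halving can appear with no true effect, and the false-finding rate ranges from about 6% to 36% instead of 5%. These figures show only how the mechanism works. The net direction is not fixed either: a stopped PPI makes attribution less likely in the intervention arm, while training about PPIs could make those GPs readier to attribute.

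A reader might go further and say that the outcome is decided by attribution, or can never be read as benefit or harm. The article supports a risk of bias, not that. Neither co-primary endpoint nor the sample size depends on this item, and the planned interim analysis does not name deficiencies among its safety parameters.

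**What to change.** Delete the reference to PPI overuse as a condition of the outcome. Define it as any new GP-documented deficiency of vitamin B12, iron, magnesium or sodium from the start of follow-up, regardless of presumed cause. Ask about it with the same question for every participant in both arms on the existing 3-monthly GP survey. If the GP's view on cause is of interest, record it as a separate item and report it descriptively.

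Optionally, add a tick-box for each analyte asking whether it was tested since the last survey, and report testing rates by arm beside the event counts. This would not equalise testing, but it would make any imbalance visible.

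The cost is a wording change and a slightly longer survey, with no added laboratory tests. The unattributed count will include some deficiencies unrelated to PPIs, which dilutes any true difference.

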#### Other endpoints

Additional endpoints will be explored and reported separately from the main trial findings, as detailed in the Dissemination section. We will evaluate cost-effectiveness by relating differences in costs and patients’ QoL over time between the new PPI deprescribing intervention and the usual care control group. Differences in direct medical costs from a Swiss statutory health insurance perspective (main analysis) during the 12-month trial time horizon will be set in relation to the difference in quality-adjusted life-years (QALYs). QALYs will be derived as the area under the survival curve, resulting from utility values calculated from EQ-5D-5L questionnaire responses. Direct medical costs will be based on healthcare resource utilisations as recorded in this trial and publicly available sources of Swiss unit costs. For costs of outpatient specialist visits, cost estimates provided by a Swiss health insurer are available. Medical resources will include but are not limited to GP and specialist consultations, endoscopies, emergency room visits, planned and unplanned hospitalisations, length of hospital stays, rehabilitation stays or any outpatient therapy visits, and/or nursing visits at home. Indirect costs arising from sick leave or reduction of employment due to worsening of symptoms will be considered in a scenario analysis.

### Study timeline

The duration of the entire project will be 60 months (5 years), with a 28-month recruitment period (ie, time from first patient included, to last patient included) and a follow-up of 12 months per participant. The study timeline is depicted in the flow chart (figure 2).

**Figure 2 F2:**
[figure not shown]
Flowchart of the DepRescribing inapprOpriate Proton Pump InhibiTors (DROPIT) trial from screening to study end.

### Sample size

The sample size calculation was based on a sequential testing procedure in line with the two co-primary endpoints (effectiveness and safety). For the effectiveness, we based the calculations on PPI discontinuation rates from previous literature^33^,^37^ (10% control group, 25% intervention group) and a Pearson χ^2^ test for superiority without continuity correction and the following assumptions: intracluster correlation coefficient of 0.05^38 39^ and a two-sided alpha of 0.05. Finally, we checked whether we achieved adequate power with the estimated sample size to demonstrate a low to medium effect size (Cohen’s d) of 0.4 for the effectiveness endpoint. For the safety, a Student’s t-test was used with the following assumptions: similar values in the two RDQ subscales (dyspepsia and GORD) per patient in both groups at the end of the trial, a non-inferiority margin of 0.5 points,^29^ a common SD of 1.3 resulting in an effect size (Cohen’s d) of 0.38, an intracluster correlation coefficient of 0.06 and a one-sided alpha of 0.025. For both co-primary endpoints, we additionally assumed a total of 80 clusters, a power of 90%, coefficient of variation of the cluster size of 0.5. We calculated a required mean cluster size of 4.0 and 4.5, and a sample size of 316 and 360 patients for the effectiveness and safety co-primary endpoints, respectively. To account for some missing data, we aim to recruit 400 patients who will be recruited in at least 80 clusters with a cluster size of between 2 and 12 participants.

### Recruitment and informed consent

GPs will screen potential participants based on the eligibility criteria during consultations or by reviewing their electronic medical records. They will ask their eligible patients if they would like to be contacted by a member of the study team. Following their acceptance, the study team will give the potential participants a call and guide them through the informed consent process. Subsequently, interested eligible patients will sign and send the informed consent to the study team by post. Once the informed consent is signed by the patient and principal investigator, the patient will be enlisted in the trial.

### Methods: assignment of interventions

#### Cluster-randomisation and group allocation

Each GP is considered as one cluster. Once a cluster is closed (ie, no more recruitment from that GP), GPs and their patients (ie, participants) are randomly assigned in a 1:1 ratio to either the intervention or the control group.

#### Blinding procedures

Given the nature of the intervention, blinding of GPs and patients will not be feasible. Thus, this is an open-label trial. However, those in the control group will remain unaware of the detailed nature of the intervention. Also, the study members involved in data collection, data analysis and statistics will not be blinded to the intervention assigned to each study arm, since information on the implementation of the intervention elements will only be collected from the intervention group.

### Methods: data collection, management and analysis

#### Data collection

Data will be collected from participants and GPs at baseline and at 3-, 6-, 9- and 12-month follow-up. Baseline data will be collected within 60 days prior to group allocation (ie, cluster randomisation). Follow-up data from participants will be collected directly through surveys (operationalised by REDCap^40 41^), or alternatively by phone, based on participants’ preference. Data from GPs will be gathered at the same time points via online surveys (REDCap).

Data collected from patients will include demographics, characteristics, attitudes toward medications, endpoint data, assessment of the implementation of the intervention elements, healthcare utilisation and safety data. From GPs, we will collect eligibility confirmation, information on patients’ medications and diagnoses, assessment of the implementation of the intervention elements and reports of serious adverse events (SAEs).

#### Data management

The data collected will be securely stored in a dedicated electronic clinical data management system (REDCap database^40 41^), with access restricted to authorised personnel only. Participants’ data will be pseudonymised, with personally identifiable information stored separately, except for email addresses used for automatic online survey distribution. In the event of study withdrawal or on study completion, the email addresses used for the automatic survey release will be removed. Regular data reviews will ensure the quality and completeness of the collected data. After the legally required retention period, the study data will be fully anonymised.

#### Statistical analysis

##### Statistical analyses for co-primary endpoints

To address the effectiveness, we will first quantify the change in prescribed PPI dose over the 12-month follow-up period. This will be done in two steps: (1) estimating the average PPI dose over the 12 months of follow-up, by dividing the area under the curve by the observation time and (2) calculating the relative change from baseline as one minus the ratio between the average prescription and the baseline prescription. Subsequently, the difference in the change in prescribed PPI dose between the control and intervention group will be calculated using a linear model, adjusted for the baseline dose and including a random effect for the cluster. We will use an intention-to-treat (ITT) analysis as primary analysis, and a per-protocol analysis as a secondary approach.

To address safety, the difference in the change in upper gastrointestinal symptoms between the two groups will be calculated with a repeated-measures linear mixed-effects model, adjusted for baseline values, and including the intervention group, the timepoint, and the interaction between group and timepoint as fixed effects. Effects of the cluster and participant will be added as random effects. We will conduct both ITT and per-protocol analyses. To claim success for the safety co-primary endpoint, both ITT and per-protocol analyses need to meet non-inferiority.

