### Limitations

Neither participants nor GPs in the intervention group or study team members/data analysts will be blinded due to the trial design. The data collected through the online survey by the participants heavily depend on the response rate. To the best of our ability, we will try to send online reminders to both participants and GPs to complete the survey.

One could hypothesise that the GPs participating in a deprescribing study may be more attentive to reducing inappropriate prescribing. However, in the study by [name] *et al* from our team, we observed that when GPs were instructed to actively identify inappropriate PPIs in patient records, only 35% of the inappropriate PPIs were stopped or reduced after 12 months, while over 60% remained unchanged.^24^ Reasons for a failed deprescribing included lack of discussion with patients, their unwillingness to stop, and fear of recurrence of symptoms. Therefore, it cannot be excluded that an increased awareness among control group patients will bias the trial results towards the null, but the effect is likely to be small.

Each GP is treated as a separate cluster and GPs are requested to keep confidentiality with colleagues. This is particularly relevant when several trial GPs work in the same practice. Otherwise, a contamination across GP clusters may potentially bias the trial results toward the null hypothesis, underestimating the intervention effect. However, GPs are used to maintaining confidentiality among colleagues and have little time to discuss the trial with peers, thus we trust that group contamination will be minimal.

In Switzerland, low dose PPI are available over the counter in pharmacies. While we will ask participants to report any self-administered medications that were not prescribed, we cannot completely control whether they purchase and use PPIs independently without reporting them. However, this issue is not expected to differ between the two groups.

There might be the possibility of a slight reporting bias as the participant surveys include questions about upper gastrointestinal symptoms. Therefore, participants could be more aware of upper gastrointestinal problems during the trial period and report these more frequently.

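### The effectiveness model's only covariate is baseline dose, already the outcome's denominator; prespecifying baseline RDQ (and attitudes, if measured at baseline) would probably add a little precision

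*Protocol article*

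**What the plan says.** Under Statistical analyses for co-primary endpoints, the effectiveness outcome is obtained by "calculating the relative change from baseline as one minus the ratio between the average prescription and the baseline prescription". The group difference is then estimated "using a linear model, adjusted for the baseline dose and including a random effect for the cluster". No other covariate is named. The safety endpoint in the same section uses a "repeated-measures linear mixed-effects model, adjusted for baseline values", so a baseline RDQ exists for each participant who answered it.

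Under Data collection, "Baseline data will be collected within 60 days prior to group allocation", and "Data collected from patients will include demographics, characteristics, attitudes toward medications, endpoint data". No instrument or time point is given for the attitude items.

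Under Limitations, the protocol describes an earlier study by the team in which most inappropriate prescriptions stayed unchanged: "Reasons for a failed deprescribing included lack of discussion with patients, their unwillingness to stop, and fear of recurrence of symptoms".

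**The concern.** Covariate adjustment in a linear model pays off to the extent that the covariates predict the outcome. Here the single covariate has already been used to scale the outcome. If the proportional reduction does not vary with starting dose, adjusting for it removes no residual variance.

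The protocol meanwhile holds, or probably holds, baseline measurements related to two of the three reasons it gives for failed deprescribing. Symptom burden bears on fear of recurrence, and attitudes bear on unwillingness to stop. The third reason, lack of discussion, has no counterpart among them. Adding prespecified baseline covariates to a linear model leaves the estimated quantity, the mean difference in relative change, unchanged. What is at stake is the width of one confidence interval.

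**Working it through.** **Inputs from the Sample size section.** Discontinuation rates "10% control group, 25% intervention group"; ICC 0.05 "and a two-sided alpha of 0.05"; check effect size d = 0.4; 80 clusters; coefficient of variation of cluster size (CV) 0.5; 90% power; required 316 (effectiveness) and 360 (safety); recruitment target 400.

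**Assumption not in the documents.** R², the share of residual outcome variance explained by the added covariates beyond baseline dose, ranges from 0 to 0.10. The ICC is held at 0.05.

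**Step 1: reproduce the plan's figure.** The pooled two-proportion formula without continuity correction, at 10% vs 25%, gives 132.8, rounded up to 133 per arm. The design effect is DE = 1 + ((1 + CV²)m − 1) × ICC. With m = 4 it is 1 + (1.25 × 4 − 1) × 0.05 = 1.20. The total is 2 × 133 × 1.20 = 319, against 316 stated. For safety (margin 0.5, SD 1.3, ICC 0.06, m = 4.5), 2 × 143 × 1.2775 = 365, against 360 stated. Both agree within 3%.

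**Step 2: power with and without added covariates.** Power = Φ( [0.4/√(1 − R²)] × √(N/DE)/2 − 1.96 ), with m = N/80. DE is 1.197 at 316, 1.231 at 360 and 1.2625 at 400. Example at N = 400, R² = 0: √(400/1.2625) = 17.80; 0.4 × 17.80/2 = 3.56; 3.56 − 1.96 = 1.60; Φ(1.60) = 94.5%.

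| Assumed R² | SE change | Power, N = 316 | N = 360 | N = 400 | 400/(1 − R²) |
|---|---|---|---|---|---|
| 0 | 0 | 90.14% | 92.78% | 94.52% | 400 |
| 0.05 | −2.5% | 91.53% | 93.93% | 95.47% | 421 |
| 0.10 | −5.1% | 92.86% | 95.00% | 96.35% | 444 |

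The last column shows the gain as an equivalent number of patients: about 21 at R² = 0.05 and 44 at R² = 0.10.

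**Step 3: does baseline dose explain anything once the outcome is a ratio?** This was an illustrative simulation with assumed baseline doses of 20, 40 and 80 mg in proportions 40:50:10, 20% stopping, and change at a random time in the year. Where the chance of halving did not depend on dose, baseline dose explained 0% of the outcome variance. Where halving occurred in 30% of those on 40 mg or more and in nobody below that, it explained 1.2%. Where halving rose with dose (5%, 25%, 50%), it explained 2.0%. These scenarios only illustrate the statistical point and say nothing about how doses should be managed.

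**The case against.** The strongest case against is that the model is sound as it stands. It is prespecified and includes the cluster effect, randomisation protects it from bias, and it has adequate power. The unseen analysis plan may add covariates. All of that is accepted. The point concerns only the covariate set that the protocol itself fixes.

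Three stronger readings are tempting, and the documents support none of them:

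- A reader might infer that adjusting for baseline dose is empty because the outcome has been divided by it. Dividing does not remove dependence. The eligibility criteria admit both patients without an indication and patients with an indication on too high a dose, so proportional change may differ by starting dose. Step 3 found small but non-zero explained variance in two of three scenarios.
- A reader might infer that the protocol identifies predictors of failure and ignores them. The Limitations section lists reasons reported in another study. It gives no measured baseline predictor and no strength of association. Baseline RDQ is measured while patients take a daily PPI and is not the same as fear of recurrence.
- A reader might infer that precision is certainly being lost. No R² appears anywhere in the protocol. If the scores are unrelated to the outcome, nothing is lost.

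Two further objections stand. That attitudes are measured before allocation is inferred from the general schedule; the same list contains items on implementing the intervention, which cannot precede allocation. Also, the patient scores come from surveys that depend on response, while medication data come from GPs. Under the protocol's available-case approach, a missing baseline score would remove a participant from the effectiveness analysis unless a rule prevents it.

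Chance imbalance is not a separate harm. With about 80 randomised units it can be larger than with 400, but it averages zero and the confidence interval allows for it.

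**Conclusion.** The point holds as a modest, optional improvement. The protocol fixes a one-covariate model for a co-primary endpoint, that covariate is already the outcome's denominator, and at least one plausible prognostic variable, baseline RDQ, is available before allocation and unused there. The likely benefit is small: no more than about 1.8 percentage points of power at 400 patients (94.52% to 96.35%) and up to 5% off the standard error. This rests on an assumed R² of 0 to 0.10, the protocol's d = 0.4, and an unchanged ICC of 0.05. Even at 316 patients the dose-only model reaches 90.1%, so the trial does not depend on the change. It is neither an error nor a source of bias.

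**What to change.** In the effectiveness model, keep baseline dose and the cluster random effect. Add baseline RDQ as a fixed covariate, and add the attitude score if it is confirmed to be measured at baseline. Name the exact scores before any outcome data are seen; this matters because the protocol says the analysts are not blinded. State that missing baseline covariate values are filled by single or mean imputation so that no participant is dropped. Report the dose-only model as a supporting analysis.

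The cost is a short addition to the analysis plan, up to two degrees of freedom if one RDQ summary and one attitude score are used (one more if the two RDQ subscales enter separately), and the missing-covariate rule. No new data are needed for RDQ. For attitudes, only the timing needs confirming.
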